**Table 2.0 – Expected Power**

| Outcome Control | Outcome Intervention | % Difference | Power |
|-----------------|----------------------|--------------|-------|
| 0.25            | 0.15                 | 0.10         | 0.94  |
| 0.25            | 0.2                  | 0.05         | 0.39  |
| 0.25            | 0.25                 | 0.0          | NA    |
| 0.3             | 0.15                 | 0.15         | 0.999 |
| 0.3             | 0.25                 | 0.05         | 0.35  |
| 0.35            | 0.15                 | 0.2          | ~1    |
| 0.35            | 0.2                  | 0.15         | 0.997 |
| 0.35            | 0.25                 | 0.1          | 0.87  |

Based on previous work by our group, we assume a 10% loss to follow up ( $784/0.90 = 870$ ), 5% drop out, and 3% drop in (caregivers who are provided with ondansetron outside the study protocol) rate ( $870/(0.92)^2 = 1030$ ). Thus, the total number randomized (final sample size) will be 1030.

## 9.3 POPULATIONS FOR ANALYSES

**Screening Population:** The screening population includes all patients who are screened for eligibility in to the trial, regardless of randomization into the trial or treatment status. This population represents all patients who meet inclusion criteria outlined in the study protocol and who are screened in real-time by study staff at the participating site. This population will be used for reporting of study flow per CONSORT guidelines.

**Intention-To-Treat Population:** The Intention-to-Treat (ITT) population includes all participants who are randomized into the trial, regardless of adherence to the protocol, including, for example, participants who receive no study drug. The ITT population will be used for the primary efficacy analyses in the study, as well as for main efficacy analyses of secondary outcomes. All analyses using the ITT population will be based on each participant's assigned treatment arm, regardless of treatment actually received.

**Safety Analysis Population:** The safety analysis population will include a subset of participants who took any doses of the study medication. A sub-analysis will be performed including only those who took 3 or more doses to assess the impact of multiple doses of ondansetron on diarrhea (and other safety outcomes). Reporting of results will be summarized according to treatment received. This population will be used for analysis of adverse events to examine safety outcomes.

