A recent small study found that 24% of pediatric patients who were treated with a single dose of ondansetron for acute gastroenteritis in the ED reported experiencing recurrent emesis within 24 hours of discharge. We hypothesize that the use of a physician-dispensed, as needed home dosing regimen of ondansetron given to patients (in anticipation of recurrent emesis and risk of dehydration) may prevent a return to the ED. While a small 2010 study found no reduction in ED revisits after discharging patients’ home with a written prescription for ondansetron, the authors caution that they did not track the number of patients who actually filled their prescriptions. In 2002, Ramsook et al. conducted a single-centre, double-blinded, placebo-controlled trial involving 145 children, comparing six doses of ondansetron/placebo administered every 8 hours for two days (scheduled). Vomiting was reduced after the first dose was administered; however, no further benefit was seen following discharge (vomiting occurred in 42% administered ondansetron versus 46% administered placebo at 24 hours). In addition, at the 24 hour and 48 hour follow-ups, the median number of vomiting episodes remained zero, with no statistically significant difference between groups. During the 48 hours following ED discharge, children administered ondansetron had threefold more diarrhea than those in the placebo group (mean 7.7 versus 2.3 episodes). The revisit rate was also higher in the ondansetron group ( $P=0.05$ ). Of the four patients with revisits in the ondansetron arm, two returned with persistent vomiting and the other two with persistent diarrhea. Interestingly, providing a home dose of ondansetron to patients by the ED physician as part of discharge planning may/ promote compliance on an outpatient basis.

A second double-blinded, placebo-controlled trial of relevance was published by Yilmaz et al. in 2010, in which the authors provided participants ( $N=109$ ) with ondansetron/placebo every 8 hours for a total of 24 hours. In this study, although ondansetron administration reduced the frequency of vomiting following discharge (mean of 1.7 versus 0.2 episodes over 24 h;  $P<0.001$ ), its administration was also associated with an increase in the number of

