## 4 STUDY DESIGN

### 4.1 OVERALL DESIGN

We will conduct a Phase III multi-centre, 2-arm, placebo-controlled, double-blind, parallel design randomized controlled trial comparing the effectiveness and adverse event profile of multiple dose (as needed) oral ondansetron compared with placebo when administered to children with acute gastroenteritis (AGE)-associated

vomiting following ED discharge. The study will be stratified by site (6 sites) and weight (< 20kgs and ≥ 20kgs). Weight is being employed, rather than age, as dosing is weight based.

We hypothesize that the administration of ondansetron post-ED discharge will be associated with improved outcomes as compared with placebo.

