#### 6.1.2 DOSING AND ADMINISTRATION

Participants will be randomized to receive either **ondansetron oral solution at a dosing rate of 0.15mg/kg** or an identical placebo oral solution (containing no active ingredients). Ondansetron oral solution will be provided in 4mg/5mL concentrations.

Study medication will be provided to the caregiver of the participant in sufficient quantity to last 48 hours. Medication can be administered **every 8 hours (q8h), to a maximum of 3 times a day (24 hour period (TID))**, as deemed necessary by the participant's caregiver(s).

Participants will not be required to take all 6 doses of the study intervention provided. They will receive doses based on need, as determined by the participant's caregiver. Caregivers will be asked to return unused study medication to the study team. All unassigned study medication will be returned to the study pharmacy for destruction.

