#### 6.4 STUDY INTERVENTION COMPLIANCE

After randomization and treatment assignment, the qualified research team member will complete a study medication dispensation form which contains the blinded kit number, expiration date, participant study ID, participant weight and age at time of enrollment, dose dispensed, the name and signature of the dispensing staff member, and the date and time of dispensation.

A drug accountability log will also be maintained at all participating institutions containing the initials of the qualified research team member dispensing the intervention to the participant caregiver, the kit number used, the accompanying participant study ID and date and time of dispensation.

The qualified research team member will demonstrate to the caregiver how to measure and dose the study medication. The exact volume in milliliters of the 4mg/5mL solution will be calculated by the research team member using REDCap prior to the caregiver leaving the ED.

The caregiver will be instructed to provide one dose every 8 hours to a maximum of 3 doses in a 24 hour period for 48 hours after discharge from the ED, as they feel their child requires the intervention. **The caregiver may choose to administer a minimum of zero to a maximum of six doses (excluding vomited doses) to the participant. If the caregiver does not administer any doses of the study intervention; the participant is still considered compliant with the study protocol.**

The number of doses administered to the participant by the caregiver will be recorded via telephone or email questionnaire performed 24 and 48 hours after enrollment (*Time 0 – Consent Date and Time*). Caregivers will be asked to return unused study medication and/or empty bottles to the study team or to a community pharmacy for destruction after the completion of the 7 day follow up period.

The participant will be considered not compliant with the protocol if the study team is unable to contact the caregiver/participant for the follow-up schedule as detailed in the SoA (section 1.3) to a maximum of 21 days after enrollment.

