#### 9.4.4 SAFETY ANALYSES

**Secondary safety outcomes** will be obtained via participant follow-up questionnaires performed 24, 48, and 168 hours (7 days) after enrollment (Time 0 – consent date and time).

Summaries of incidence rates (frequencies and percentages), intensity, and relationship to study of individual AEs by System Organ Class and Preferred Term (MedDRA) will be prepared. All AEs beginning after randomization but before discharge will be included. Basic summaries by assigned groups will be prepared. The DSMB may request to see more detailed tables. The occurrence of any adverse event will be considered as a dichotomous outcome.

To obtain SAE, palpitation, pre-syncope/syncope, chest pain, and arrhythmia data; each questionnaire will contain open ended, non-symptom specific questions where caregivers can provide the study team with information about their child's illness or any other concern they may have. Any response to this question will result in a trained study team member discussing the information provided in more detail via telephone. Any symptom or condition that meets the definition of an SAE will be categorized as such and reported appropriately.

1. **Frequency of diarrheal episodes during the 48-hours following ED disposition:** Frequency and maximal number of diarrheal episodes will be obtained by asked about presence of diarrhea on each questionnaire the caregiver completes. If diarrhea is present, further questions related to the number of episodes will be asked. Frequency will be calculated over 48 hours for all patients regardless of whether they have greater than 24 hours with no symptoms.
2. **Maximal number of diarrheal episodes in 24 hours:** Same as above – Frequency
3. **Serious Adverse Events (SAEs)**
4. **Palpitations**
5. **Pre-syncope /syncope**
6. **Chest Pain**

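### The sub-analysis of children who took 3 or more doses cannot isolate an effect of multiple doses on diarrhea: dose count is a post-randomisation result that ondansetron may change, and the bias can run either way

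*Combined protocol and SAP*

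**What the plan says.** Section 9.3 defines the safety population as children who took any study medication. It then plans a sub-analysis "including only those who took 3 or more doses to assess the impact of multiple doses of ondansetron on diarrhea", extended to other safety outcomes, with results summarised by the treatment actually received.

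Dosing is not fixed. Section 6.1.2 says of participants: "They will receive doses based on need". Section 6.4 says: "The caregiver may choose to administer a minimum of zero to a maximum of six doses (excluding vomited doses) to the participant". The need is judged by the caregiver. Section 4.1 states the expected direction: "We hypothesize that the administration of ondansetron post-ED discharge will be associated with improved outcomes as compared with placebo".

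Section 9.4.4 names two diarrhea safety endpoints. The 48-hour count is compared with a Poisson generalized linear model adjusted for stratification, and the 24-hour maximum with a Mann-Whitney test. The 48-hour count covers the same period in which doses are given. For adverse-event tables the same section says: "Basic summaries by assigned groups will be prepared".

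Nothing in the plan adjusts for selection on dose count, calls the subset non-randomised, or cautions about reading it.

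**The concern.** The stated purpose is causal: to learn what several doses do to diarrhea. The comparison is restricted by something that happens after randomisation. If ondansetron stops vomiting, some active-arm children stop needing doses and never reach three, while similar placebo children do. The two groups of three-dose takers then differ in illness before any effect on stools is considered.

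Diarrhea is the harm that the trial has to weigh against benefit (Section 4.2). Section 2.2 cites two earlier trials with more diarrhea on ondansetron: means of 7.7 versus 2.3 episodes in one and 5.0 versus 4.3 in the other. The second is a ratio of 5.0/4.3 = 1.16. A selection artefact of that size could be read as replication, and one in the other direction as reassurance.

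**Working it through.** The plan gives no figure for this sub-analysis, so there is none to reproduce. The check asks what ratio the subset shows when the drug has no effect on diarrhea.

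**Inputs from the documents.** Up to six doses, 8 hours apart (Section 6.4). 1030 randomised and 10% lost to follow-up (Section 9.2): 1030 × 0.90 = 927, about 464 per arm. Two earlier results on vomiting after discharge (Section 2.2) disagree:
- "vomiting occurred in 42% administered ondansetron versus 46% administered placebo at 24 hours", a ratio of 42/46 = 0.91.
- "mean of 1.7 versus 0.2 episodes over 24 h", placebo first, a ratio of 0.2/1.7 = 0.12.

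**Assumptions not in the documents.** The share of placebo children reaching three doses (15 to 50%); the factor RR by which the drug multiplies dose need (0.91, 0.67, 0.40); and the severity-stool slope c (−0.3, 0, 0.3, 0.6).

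**Model.** Each child has a latent severity U. In each of six windows a placebo child takes a dose with probability p(U), which rises with U. An active child has probability p(U) until the first study dose and RR × p(U) after it. The stool mean is exp(b + cU), with the same b and c in both arms. The subset ratio is

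E[exp(cU) | 3+ doses, active] / E[exp(cU) | 3+ doses, placebo].

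**Why one or more doses is safe in this model.** P(at least 1 dose | U) = 1 − (1 − p)^6 in both arms. RR does not enter, so the ratio is 1.00. This needs blinding to hold, so that the first study dose is chosen before study drug can act.

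**Why three or more is not, by hand with RR = 0.40.**
- Child with p = 1. Placebo: certain to reach three. Active: first dose, then at least 2 of 5 at 0.40, which is 1 − 0.6^5 − 5(0.4)(0.6^4) = 1 − 0.078 − 0.259 = 0.663.
- Child with p = 0.5. Placebo: 1 − (1 + 6 + 15)/64 = 0.656. Active: sum over the window of the first dose, later windows at 0.20: 0.5(0.263) + 0.25(0.181) + 0.125(0.104) + 0.0625(0.040) = 0.192.

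Relative to placebo, the active arm keeps 0.663/1 = 66% of the sickest children but only 0.192/0.656 = 29% of the milder ones. Its three-dose subset is sicker.

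**Simulation, no drug effect on diarrhea** (1,000,000 children per arm, 30% of placebo children at three or more doses, dose-need slope 2). Expected numbers use 464 per arm; placebo is 464 × 0.30 = 139.

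| RR | Active share at 3+ | Active n | c = −0.3 | c = 0 | c = 0.3 | c = 0.6 |
|---|---|---|---|---|---|---|
| 0.91 | 27.9% | 129 | 0.99 | 1.00 | 1.01 | 1.02 |
| 0.67 | 21.1% | 98 | 0.97 | 1.00 | 1.04 | 1.07 |
| 0.40 | 11.0% | 51 | 0.94 | 1.00 | 1.07 | 1.14 |

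Over the whole grid, positive c gives about 1.01 to 1.14 and c = −0.3 gives about 0.94 to 0.99. The ratio is 1.00 in all randomised children and in takers of one or more doses.

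**Other structures, same null.**
- Doses triggered by vomiting, with 30%, 50% or 70% less vomiting on drug: about 1.08, 1.16 and 1.29. A version with lognormal severity and slopes of 0.5 to 0.7 gives 1.06 to 1.09, 1.12 to 1.18 and 1.22 to 1.33.
- Vomit-triggered dosing with slope 0.6, but 20% of caregivers in both arms dosing every 8 hours regardless: 0.98, 0.96 and 0.90. Schedule-dosers reach three doses whatever the drug does, so they make up more of the active subset and pull its average severity down.
- Negative severity-stool link, other settings: 0.89 to 0.99.

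**Chance of a false harm signal, if the subset were tested.** With positive c, correct variance and a nominal one-sided 2.5%: about 3% at RR 0.91, 3 to 8% at RR 0.67, and 4 to 13% at RR 0.40.

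**The case against.** The strongest reply is that little depends on this analysis. Section 9.3 calls it a sub-analysis and names no test for it. The any-dose comparison is already planned. An all-randomised diarrhea comparison appears to be planned too: diarrhea duration and frequency are in the Holm family (Section 9.4.1), diarrhea episodes are in the text of the first secondary outcome (Section 9.4.3), and Section 9.3 assigns the main analyses of secondary outcomes to the intention-to-treat population. That stands, and it limits the importance of the point. It does not settle the 48-hour count and the 24-hour maximum, which Section 9.4.4 lists as safety outcomes without clearly specifying an all-randomised comparison.

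A second reply is that the multi-dose question matters and that zero doses counts as compliant, so an all-randomised comparison dilutes any multi-dose harm. This is also true. But a diluted estimate is still a valid between-arm comparison, and the subset estimate is not.

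A reader might go further and infer that the bias must run toward false harm. The documents do not support that. They give no vomiting-diarrhea link, they leave the dosing trigger to the caregiver, and Section 2.2 describes home doses given in anticipation of vomiting. Nor do they show that ondansetron changes dose need: that follows from the trial's hypothesis, and the two earlier trials disagree.

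**Conclusion.** The point holds as a bias of unknown sign and modest to moderate size. Under the null, the ratio among takers of three or more doses is about 1.02 to 1.3 if doses follow vomiting and sicker children have more of both symptoms. It is about 0.9 to 1.0 if the link is negative or some caregivers dose on schedule. In the vomiting-driven model it is within 1 to 2% of 1.00 if dose need falls by only about 9%. All of these rest on assumed dosing behaviour, drug effect and severity links.

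Three stronger readings should be resisted:
- This is not the trial's main safety analysis.
- Selection of this size could not by itself produce an excess like 7.7/2.3 = 3.3.
- The any-dose population does not share the fault, provided blinding holds.

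The difference between reporting by treatment received (Section 9.3) and by assigned group (adverse-event tables, Section 9.4.4) is a separate, minor inconsistency. It neither causes nor cures the selection on dose count.

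**What to change.** In Sections 9.3 and 9.4.4:

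1. State that between-arm inference on 48-hour diarrhea frequency and on the 24-hour maximum is made in all randomised children by assigned arm, with the planned population of one or more doses alongside.
2. Report diarrhea by number of doses taken, including three or more, as descriptive and non-randomised, with no between-arm test and no causal wording.
3. Separately, reconcile reporting by treatment received with reporting by assigned group.

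The cost is a few lines of text and no new data. The trial gives up a direct comparison in multi-dose takers, and the all-randomised comparison dilutes any effect confined to them. If a multi-dose estimate is still wanted, a principal-stratum or instrumental-variable analysis could be pre-specified with its assumptions stated.

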## 9.4 STATISTICAL ANALYSES

### 9.4.1 GENERAL APPROACH

For the primary outcome, the significance level will be set at 0.05. The overall significance level for statistical tests on the secondary outcomes will be set at 0.05.

To control the overall significance level for the secondary outcomes, the significance level will be adjusted for multiple comparisons. Vomiting and diarrhea duration, vomiting and diarrhea frequency, proportion with vomiting, unscheduled healthcare provider visits, intravenous rehydration, and caregiver satisfaction will be subject to Holm's stepdown procedure. Specifically, the smallest of the eight p-values will be compared to a significance level of  $0.05/8$ . If significance is reached, the next-smallest p-value will be compared to  $0.05/7$ , and so on. The final p-value of the six will be compared to 0.05, assuming that all others are significant. Confirmatory and tertiary outcome results will not be adjusted for multiple comparisons, as these are more exploratory in nature.

A 95% confidence interval will be reported around estimates of the treatment effects of the primary and secondary outcomes.

All analytical models will be evaluated and adjustments will be made if any assumptions appear to be seriously violated.

Publication of the primary results will include reporting of key baseline characteristics overall, and by assigned treatment arm (active or placebo). These will include, but will not be limited to,

- Gender
- Age
- Season
- Weight

- Primary care physician access
- Daycare attendance
- Receipt of rotavirus vaccine
- Vomiting and diarrhea duration and frequency
- Presence of fever
- Prior ED visits, IV rehydration, hospitalization
- Baseline MVS
- Duration of symptoms prior to enrollment (<48 hours vs. 48 hours or more)
- Antibiotic usage during the 14 days prior to ED visit
- Hydration assessment (Clinical Dehydration Scale score)
- Need for hospitalization from initial ED visit

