| Endpoints:                                              | 
Primary Endpoint: Post-index visit MVS score.
 
Secondary Endpoints will include:
 
 
1. Vomiting: Frequency, Duration, Proportion (i.e. yes/no)
 
2. Health care use: Emergency Department, Primary Care
 
3. Intravenous rehydration
 
4. Caregiver Satisfaction with Therapy Provided: Likert Scale
 
                                                                                                                                                                                                                                                                                                                                                                                                                                   |
| Study Population:                                       | Children and youth, age 6 months to 17.99 years will be enrolled at six (6) Canadian Emergency Departments. The total number of participants recruited will be 1030.                                                                                                                                                                                                                                                                                                                                                                                                                                                                                                                                                                                                                                                                  |

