#### 9.4.3 ANALYSIS OF THE SECONDARY ENDPOINT(S)

**Secondary outcomes** and how they will be assessed can be found below:

1. **Frequency of vomiting from study enrollment to day 7:** The total number of episodes of vomiting and diarrhea related to the presenting illness will be compared between groups (active and placebo). This data will be obtained from the study questionnaires performed on Day 0, 24, 48, and 168 (7 days) hours after enrollment. Questionnaires (telephone or email) will contain questions regarding vomiting presence, number of episodes, and vomiting cessation date and time. Frequency will be defined as the total number of episodes across the study duration and will not consider differences in the vomiting duration across participants.
2. **Duration of vomiting:** The total number of days the participant experiences vomiting from Day 0 to Day 7. This data will be obtained from the study questionnaires performed on Day 0, 24, 48, and 168 (7 days) hours after enrollment. Questionnaires (telephone or email) will contain questions regarding vomiting presence, number of episodes, and vomiting cessation date and time. A participant with a 24-hour break in symptoms will be assumed to have ceased vomiting.
3. **Proportion of participants who experience vomiting within 7 days of enrollment:** The proportion of participants will be determined using data from the participant questionnaires performed 24, 48, and 168 hours after enrollment (Time 0).
4. **Proportion of participants who require an unscheduled health care provider visit within 7 days of enrollment:** Return visits for unscheduled care to a health care provider related to vomiting, diarrhea, dehydration, fever, abdominal pain, or fluid refusal within 7 days, not including scheduled visits (e.g. reassessments, vaccinations, etc.) will also be measured using follow up questionnaires 24, 48, and 168 hours after enrollment. Return to care data will be confirmed by reviewing the participant's hospital chart. Not all data within a patient's medical record will be available to the research team therefore the questionnaires will be the primary source of this data.

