5. **Proportion of participants who require intravenous rehydration:** If the participant required an unscheduled health care visit (see #4 above), the participant will be asked additional questions related to intravenous (IV) insertion, treatment course, and disposition. Intravenous fluids administered at the index visit will not be included as part of this outcome.
6. **Caregiver satisfaction as measured by a 5-point Likert scale in the 48 hours following ED disposition:** Caregiver satisfaction with the therapy provided (oral ondansetron or placebo) in the 48 hours following ED disposition. This will be measured using a 5 point Likert scale on the questionnaire administered 168 hours after Time 0.

The analysis of secondary outcomes will be undertaken as detailed below:

1. **Frequency of vomiting from study enrollment to Day 7:** The total number of episodes of vomiting and diarrhea related to the presenting illness will be compared between groups (active and placebo) using a generalized linear model to compare differences between Poisson rates whilst adjusting for stratification.

2. **Duration of vomiting :** The total number of days the participant experiences vomiting from Day 0 to Day 7 will be compared using the Van Elteren test, stratified by center and duration of symptoms (pre-enrollment). If a number of patients still experience symptoms at the 7-day follow-up questionnaire, this will be tested using a suitable procedure to take account of censoring such as median regression or additive hazard models. Additional analyses involving this outcome will include linear regression models that adjust for possible effects of baseline characteristics.
3. **Proportion of participants who experience vomiting within 7 days of enrollment:** The proportion of participants with vomiting following enrollment will be compared using Mantel-Haenszel test stratified by site and weight.
4. **Proportion of participants who require an unscheduled health care provider visit within 7 days of enrollment:** The proportion of participants who require an unscheduled health care provider visit within 7 days of enrollment will be compared using Mantel-Haenszel test stratified by site and weight.

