## 7. Arrhythmias

Serious Adverse Events/Deaths will be reported separately in a similar fashion to the more general AE reports. In addition, narratives will be available for each event.

The analysis of safety outcomes will be undertaken as detailed below:

1. **Frequency of diarrheal episodes during the 48-hours following ED disposition:** The total number of episodes of diarrhea related to the presenting illness will be compared between groups (active and placebo) using a generalized linear model to compare differences between Poisson rates whilst adjusting for stratification.
2. **Maximal number of diarrheal episodes in 24 hours:** To test whether this outcome differs between the active and placebo treatments, we will use a Mann-Whitney U-test.
3. **Serious Adverse Events (SAEs):** The frequency of SAEs will be reported for both active and placebo groups. No formal testing will be undertaken.
4. **Palpitations:** The frequency of palpitations will be reported for both active and placebo groups. No formal testing will be undertaken.
5. **Pre-syncope /syncope:** The frequency of pre-syncope/syncope will be reported for both active and placebo groups. No formal testing will be undertaken.
6. **Chest Pain:** The frequency of chest pain will be reported for both active and placebo groups. No formal testing will be undertaken.
7. **Arrhythmias:** The frequency of arrhythmias will be reported for both active and placebo groups. No formal testing will be undertaken

---

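### Section 9.4.1 sizes the Holm family for the secondary outcomes as eight and then as six, and its two diarrhea members are not properly specified

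*Combined protocol and SAP*

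**What the plan says.** Section 9.4.1 fixes the family-wise level: "The overall significance level for statistical tests on the secondary outcomes will be set at 0.05". It names the members of the Holm family as "Vomiting and diarrhea duration, vomiting and diarrhea frequency, proportion with vomiting, unscheduled healthcare provider visits, intravenous rehydration, and caregiver satisfaction". Counting duration and frequency separately for vomiting and for diarrhea, that makes eight. The procedure then opens consistently with that count: "the smallest of the eight p-values will be compared to a significance level of" 0.05/8, with 0.05/7 next. It closes with a different count: "The final p-value of the six will be compared to 0.05, assuming that all others are significant".

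The endpoint lists elsewhere give six. The synopsis has "1. Vomiting: Frequency, Duration, Proportion (i.e. yes/no"), followed by health care use, intravenous rehydration and caregiver satisfaction; Table 1.0 repeats this. Section 9.4.3 numbers six outcomes, the last being "Caregiver satisfaction as measured by a 5-point Likert scale in the 48 hours following ED disposition". None of the six is headed as a diarrhea outcome.

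Diarrhea enters the plan in three other places:

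- Section 9.4.3 item 1 is headed as vomiting frequency to Day 7, but its text reads "The total number of episodes of vomiting and diarrhea related to the presenting illness will be compared between groups (active and placebo").
- Section 9.4.4 gives diarrhea frequency its own analysis as a safety outcome over the 48 hours after ED disposition: "The total number of episodes of diarrhea related to the presenting illness will be compared between groups (active and placebo").
- Section 9.4.2 defines diarrhea duration as one of the seven score components.

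**The concern.** The Holm rule decides which secondary findings may be called significant, and it needs a fixed list of tests settled in advance. Here one paragraph gives two family sizes. The smaller size agrees with every endpoint list in the document and the larger agrees with the outcomes named in the paragraph, so the word six cannot simply be dismissed as a slip.

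The two outcomes that make up the difference are also the two least well defined. Someone running the eight-step version would have to choose a test for diarrhea duration. For diarrhea frequency, they would have to choose the time window, whether diarrhea is counted alone or with vomiting, and the analysis population. Those choices, and the choice between six and eight, should not be open once results are visible. A smallest p-value of 0.007, for example, would yield no secondary claim under one reading and at least one under the other.

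**Working it through.** **Inputs.** Family-wise level 0.05, eight named outcomes, first two steps 0.05/8 and 0.05/7, and the closing reference to six (all section 9.4.1). Six secondary efficacy outcomes (synopsis, Table 1.0, section 9.4.3): three for vomiting, plus unscheduled visits, intravenous rehydration and satisfaction, so 3 + 1 + 1 + 1 = 6. Health care use is counted once, as in secondary objective 2 and section 9.4.3 item 4.

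**Step 1: reproduce the stated thresholds.** Holm compares the i-th smallest of m p-values with 0.05/(m − i + 1).

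| Step | m = 8 | m = 6 |
|---|---|---|
| 1 | 0.00625 | 0.00833 |
| 2 | 0.00714 | 0.01000 |
| 3 | 0.00833 | 0.01250 |
| 4 | 0.01000 | 0.01667 |
| 5 | 0.01250 | 0.02500 |
| 6 | 0.01667 | 0.05000 |
| 7 | 0.02500 | – |
| 8 | 0.05000 | – |

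The stated first, second and last steps match m = 8 exactly. The last step is 0.05 for any m, so it does not tell the two sizes apart. Only the word six fails to fit.

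**Step 2: type I error of the stated steps at the first step.**

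- Eight tests at 0.05/8: bound 8 × 0.00625 = 0.05; if independent, 1 − (1 − 0.00625)^8 = 0.0489.
- Six tests at 0.05/8: bound 6 × 0.00625 = 0.0375; if independent, 1 − (1 − 0.00625)^6 = 0.0369. This is conservative.
- Eight tests at 0.05/6, which the plan does not propose: bound 8 × 0.00833 = 0.0667; if independent, 0.0648. The family therefore cannot hold eight outcomes and start at 0.05/6.

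**Step 3: what the choice costs in power.** The documents give no power for any secondary outcome, so 80% and 90% at a two-sided 0.05 are assumptions. The shift is 1.960 + 0.842 = 2.802 for 80% and 1.960 + 1.282 = 3.242 for 90%. The two-sided critical values are 2.734 at 0.00625 and 2.638 at 0.00833.

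- Assumed 80%: Φ(2.802 − 2.734) = 52.7% with eight; Φ(2.802 − 2.638) = 56.5% with six.
- Assumed 90%: Φ(3.242 − 2.734) = 69.4% with eight; Φ(3.242 − 2.638) = 72.7% with six.

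The difference is 3.8 and 3.3 points, at the strictest step only.

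**Step 4: are the two extra members defined?**

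| | Diarrhea duration | Diarrhea frequency |
|---|---|---|
| Named in the Holm list (9.4.1) | yes | yes |
| Own numbered outcome in 9.4.3 | no | no; pooled with vomiting in item 1 |
| Window | score component, to Day 7 | Day 7 in 9.4.3, 48 hours in 9.4.4 |
| Test | none | Poisson model in both places, on different counts |
| Population | not stated | intention-to-treat if secondary efficacy; participants who took any dose, by treatment received, if safety (9.3) |

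**The case against.** The strongest reply is that nothing operative is wrong. Section 9.4.1 names its eight outcomes and gives 0.05/8 and 0.05/7; on that view six is a one-word error that changes no threshold. The arithmetic stands. That six is merely a leftover is a guess: the documents do not confirm it, and six matches every endpoint list.

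Several stronger readings may tempt a reader, and the documents do not support them.

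- *The significance thresholds are wrong or inflate type I error.* They are correct Holm steps for eight tests and conservative for six.
- *The sixth-smallest of eight p-values is tested at 0.05.* With five false nulls already rejected and three independent true nulls left, that would give an error of 1 − 0.95³ = 0.143, against 1 − (1 − 0.05/3)³ = 0.049 for proper Holm. But the text describes a continuing sequence whose final p-value meets 0.05, not a jump at the sixth of eight.
- *The main feared harm, more diarrhea, must clear 0.00625.* Neither section 9.4.1 nor 9.4.4 places the 48-hour safety endpoint in the Holm family. The Holm wording is closer to the Day 7 count in section 9.4.3 item 1, and the other tested diarrhea outcome, the maximum in 24 hours, is not listed. Membership remains open to question, because sections 3 and 9.4.4 label these outcomes secondary safety and section 9.4.1 exempts only confirmatory and tertiary outcomes. That is an ambiguity, not a stated rule. A fall from 80% to 52.7% would in any case be the whole cost of first-step adjustment, not the cost of this inconsistency.
- *The procedure cannot be run at all.* Diarrhea duration has a computation rule in section 9.4.2, and the other outcomes could be tested conservatively on the stated steps. What is missing is its standing as an endpoint and a named test.

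**Conclusion.** The point holds as an inconsistency in the decision rule for the secondary outcomes. The family size is given as eight and as six, the endpoint lists support six, diarrhea duration has no test, and diarrhea frequency has two competing definitions. The size is a first-step threshold of 0.00625 or 0.00833, worth about 3 to 4 points of power under the assumed 80% or 90%. The independence-based error rates assume independent tests; the bounds do not. The primary test and the sample size are untouched. It should still be settled before unblinding, because the rule governs every secondary claim.

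**What to change.** Preferred: define the Holm family in section 9.4.1 as the six secondary efficacy outcomes of section 9.4.3, with steps 0.05/6, 0.05/5, and so on to 0.05. Delete the words *and diarrhea* from section 9.4.3 item 1, in both the definition and the analysis text, so that it matches its heading. Report diarrhea frequency and duration as safety outcomes with unadjusted 95% confidence intervals, and say in section 9.4.4 that they lie outside the Holm family.

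Equally valid: keep eight, change six to eight, and give diarrhea duration and diarrhea frequency each a definition, window, population and test in section 9.4.3. Item 1 must then be split so that vomiting and diarrhea are counted separately. No threshold changes.

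Make the change before unblinding, and preferably before secondary results are tabulated by arm. Section 9.4.6 lets the data-center statisticians see results by arm with the identities masked, and masking does not hide a two-sided p-value.

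The cost is a wording amendment to the protocol and SAP. The Statement of Compliance requires ethics board review and approval of protocol amendments, so that step is included. No data collection or recruitment is affected.
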